#### Physiologic Measurements

The two measures (pain pressure, tissue stiffness) have previously been reviewed by UBC CREB and are considered to be minimal risk, in that they do not expose subjects to any risk beyond what they would typically encounter in everyday life.

Pain pressure – this test involves the gradual application of pressure to the painful site, and the test is immediately stopped when the subject reports onset of pain. This is essentially an objectified equivalent of a person gently squeezing a painful spot to localize their pain. Based on clinical experience and reasoning, this type of test is not enough to cause injury – the application of gentle pressure to a painful site is standard practice in clinical examinations.

Tendon stiffness – this test applies a force of several newtons (about the weight of a strawberry).

## **12. Statistical Considerations and Data Analysis**

The pain pressure threshold measurement will be repeated three times and the two closest measures will be used for analysis. To avoid wind up, we will wait one minute between each measure.

A repeat measures ANOVA will be used to detect the effect of time (0, 4, 12 weeks) or treatment (placebo vs active) on VISA-A score. Paired t-tests will be used to detect changes in pain, pain pressure threshold and tendon stiffness from baseline to 4 weeks. The proportion of individuals who have returned to full activity at the different timepoints will be reported as point estimates with 95% confidence intervals. The global rating of change (Likert scale) will be compared between groups using a Mann Whitney-U test.

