## **6. Study Design**

Placebo-controlled trial, random allocation in a 1:1 ratio.

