### **10.2 Secondary Outcomes**

1. Pain (Numeric Pain Rating Scale, 0 - 10)

- i. Average pain during all tendon loading activities over last week
- ii. Average pain during rehabilitative exercise over last week
- iii. Average pain at rest during last week
- iv. Current resting pain

2. Patient-reported change in symptoms (7 point scale from substantially better to substantially worse)

3. Pressure pain threshold (N) and transverse tendon stiffness (N/m) measured over the site of maximum tendon stiffness

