### Sample Size Calculation

We estimate that after 4 weeks, the placebo group will experience a clinically insignificant mean improvement of 5 (SD17) points on the VISA-A, compared to a clinically significant improvement of 15 (SD17) with diclofenac. For a two-sided t-test with alpha 0.05 and power 0.80, the required sample size is 46 per group.

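### Analysing only the two closest of three pressure-pain readings gives up precision that the median of the same three readings would keep

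*Protocol*

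**What the plan says.** Section 12 of the protocol fixes how the pain pressure threshold (PPT) is summarised at a session: "The pain pressure threshold measurement will be repeated three times and the two closest measures will be used for analysis". The next sentence sets the spacing: "To avoid wind up, we will wait one minute between each measure". No reason is given for choosing by closeness, and the way the two retained readings become one value is not stated.

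PPT is a named secondary outcome in section 10.2: "Pressure pain threshold (N) and transverse tendon stiffness (N/m) measured over the site of maximum tendon stiffness". Section 12 analyses it as a change: "Paired t-tests will be used to detect changes in pain, pain pressure threshold and tendon stiffness from baseline to 4 weeks". The selection rule therefore acts at both visits.

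The protocol gives no SD, reliability or error distribution for PPT.

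**The concern.** Two of three readings may lie close together simply by chance. When they do, the discarded third reading usually carries as much information as the two that are kept. Selecting on closeness moves the analysed value away from the mean of three by half the deviation of the dropped reading, and that movement is added noise. Participants have already given all three readings, so the information is collected and then lost.

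At stake is the precision of one secondary outcome, at both ends of its change score.

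**Working it through.** **The plan's own figure.** The only computed figure in the protocol is the sample size for VISA-A. The inputs are a difference of 15 − 5 = 10, an SD of 17, two-sided alpha 0.05 and power 0.80: n = 2 × (1.960 + 0.842)² × 17² / 10² = 45.4, rounded up to 46 per group, as stated. It does not involve PPT, and there is no PPT figure to reproduce.

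**Inputs for PPT.** From section 12: three readings, two kept by closeness, change from baseline to 4 weeks. Assumed: the two are averaged; the three errors are independent with variance s² each. The base case takes them as normal.

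**Error variance, normal case.**
- Mean of three: s²/3 = 0.333 s².
- Median of three: (1 − √3/π) s² = 0.449 s².
- Two readings fixed in advance: s²/2 = 0.500 s².
- Closest pair: its mean equals the mean of three minus d/2, where d is the deviation of the dropped reading from the mean of three. The two parts are independent, and E(d²) = (4/3) × E(cos² t) × s², with t uniform on (−π/6, π/6). E(cos² t) = 0.5 + sin(π/3)/(2π/3) = 0.9135, so E(d²) = 1.218 s². Variance = 1/3 + 1.218/4 = 0.638 s².

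Ratios: 0.638/0.333 = 1.91 against the mean; 0.638/0.449 = 1.42 against the median. The pair is also worse than two readings fixed in advance (0.638/0.500 = 1.28).

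**Other error distributions** (simulated variance ratios, 2,000,000 triplets each):

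| Error model | Pair / mean | Median / mean | Pair / median |
|---|---|---|---|
| Normal | 1.92 | 1.35 | 1.42 |
| Uniform | 2.47 | 1.80 | 1.38 |
| Lognormal, CV 10% | 1.89 | 1.34 | 1.42 |
| Lognormal, CV 30% | 1.73 | 1.26 | 1.38 |
| Lognormal, CV 50% | 1.48 | 1.12 | 1.32 |
| t, 10 df | 1.72 | 1.22 | 1.41 |
| t, 5 df | 1.46 | 1.05 | 1.39 |
| Laplace | 1.32 | 0.96 | 1.38 |
| t, 3 df | 0.98 | 0.72 | 1.35 |
| 5% of readings with 5-fold SD | 0.98 | 0.74 | 1.34 |
| 10% of readings with 5-fold SD | 0.78 | 0.60 | 1.30 |
| 5% of readings with 10-fold SD | 0.42 | 0.33 | 1.29 |
| 10% of readings with 10-fold SD | 0.39 | 0.31 | 1.28 |
| One-sided stray presses: 10% of readings shifted up by 10 SD | 1.00 | 0.89 | 1.13 |

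The pair-to-mean ratio crosses 1, but the pair-to-median ratio stays between 1.13 and 1.42. A systematic drift over the three readings, which is the wind-up that the one-minute wait is meant to prevent, is a separate case. With normal errors and a drift of 0.5 or 1 SD per reading, pair/mean is 2.14 or 2.82 and pair/median is 2.143/1.433 = 1.50 or 2.822/1.681 = 1.68.

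**Effect on the planned change score.** Let the true-change variance be f × s², with independent errors at the two visits. The variance ratio of pair to mean of three is (f + 2 × 0.638)/(f + 2 × 0.333).
- f = 4: 5.276/4.667 = 1.13.
- f = 1: 2.276/1.667 = 1.37.
- f = 0 (no true variation in change): 1.276/0.667 = 1.91.

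Against the median, with 2 × 0.449 = 0.897 in the denominator: f = 4 gives 5.276/4.897 = 1.08, and f = 1 gives 2.276/1.897 = 1.20. In terms of 100 participants, the loss against the mean is like analysing 100/1.13 = 88 (f = 4) or 100/1.37 = 73 (f = 1). The values of f are assumptions; the documents do not bear on them.

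**The case against.** The best defence of the rule is protection against stray readings. The participant presses a button as pressure rises, and anyone with resting pain must judge a first increase in pain (section 11, Visit 1). A late or early press is plausible, and keeping the two readings that agree is a recognisable guard against it. This stands to the extent that, with frequent gross outliers, the closest pair does as well as or better than the mean of three. Replacing it by the mean without thought could then make matters worse.

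It does not save the rule, because the median gives the same kind of protection at lower variance in every outlier model tried. In the one-sided model the pair has a slightly smaller upward shift (0.28 against 0.41 SD). Adding the squared shift to the variance still favours the median: 3.351 + 0.081 = 3.432 against 2.957 + 0.164 = 3.121, a ratio of 1.10.

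Four stronger readings are tempting, and the documents do not support them.
- A reader might infer that the rule nearly doubles measurement error outright. The factor 1.91 holds for independent near-normal errors, and the protocol gives no error distribution.
- A reader might infer that the analysed outcome loses that much precision. True variation between people or in change dilutes it. At a single visit, with an assumed single-reading reliability of 0.70 to 0.95, total variance rises by only 11% to 1.6%.
- A reader might infer bias between arms. The rule is the same in both arms, and section 11 says that neither investigator nor subject knows which tube was issued.
- A reader might infer that repeatability will be misreported, since two readings chosen for agreement look too consistent. The protocol plans no repeatability analysis.

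**Conclusion.** The rule is fixed in the protocol and is an inefficient summary of readings already taken. Under independent near-normal errors its error variance is 1.9 times that of the mean of three and 1.4 times that of the median. The first ratio depends heavily on the assumed distribution and can fall below 1. The second stayed within 1.13 to 1.42 across all error distributions tried, and that is the firmer ground.

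For the planned change from baseline to 4 weeks, the loss against the mean of three is about 13% to 37% in variance, for near-normal errors and a true-change variance of four times to one times the single-reading error variance. All of this presumes that the two retained readings are averaged.

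The consequence is a modest loss of precision on one secondary outcome. The VISA-A analysis and the 46 per group are unaffected. It is best treated as a free improvement rather than an error that threatens the trial.

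**What to change.** Replace the closest-pair rule in section 12 with: *At each visit, the value analysed is the median of the three pain pressure threshold readings.* If gross outlying readings are not expected, the mean of all three is the more precise choice and may be named instead. Choose one, apply it at both visits, and record the choice before unblinding.

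The cost is one sentence. No extra readings or visits are needed. If only the two retained readings have been recorded for any participant, all three should be recovered from the device software where possible.

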## **5. Hypothesis**

Individuals treated with topical diclofenac will have a greater improvement in VISA-A score at 4 weeks than those treated with placebo gel.

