## **10. Study Outcomes**

### **10.1 Primary Outcome**

VISA-A score (0-100) at 4 weeks.

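### The only VISA-A analysis in the protocol names a time effect or a treatment effect over weeks 0, 4 and 12; neither is the 4-week between-group difference in the hypothesis, and the 80% power was calculated for a different test

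*Protocol*

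**What the plan says.** Three parts of the protocol agree on the question:

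- **Section 5 (Hypothesis):** the diclofenac arm will show "greater improvement in VISA-A score at 4 weeks than those treated with placebo gel".
- **Section 10.1 (Primary Outcome):** "VISA-A score (0-100) at 4 weeks".
- **Sample Size Calculation:** it assumes that "the placebo group will experience a clinically insignificant mean improvement of 5 (SD17) points on the VISA-A". For the active arm it assumes 15 points with the same SD. It then states: "For a two-sided t-test with alpha 0.05 and power 0.80, the required sample size is 46 per group".

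Section 3 lists persistence at 12 weeks as a second, separate aim.

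The analysis in Section 12, with VISA-A as the response, reads: "A repeat measures ANOVA will be used to detect the effect of time (0, 4, 12 weeks) or treatment (placebo vs active"). No other analysis of VISA-A is given. The sentence names no treatment-by-time interaction, no 4-week contrast and no baseline adjustment.

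**The concern.** The test in Section 12 does not answer the question fixed in Sections 5 and 10.1. A time effect says that scores moved in the two arms together, which is not a drug comparison. A treatment main effect compares the arms on the average of three visits. One of these precedes treatment, so its expected difference is zero under randomisation. Another falls 8 weeks after treatment ends.

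Two things are at stake. A real 10-point benefit at 4 weeks could be diluted and missed. And because the sentence joins the two effects with an 'or' and does not say which one decides the trial, the choice among time, treatment and an unnamed interaction could be made after the data are seen. The power statement gives no protection here, because it was calculated for another test.

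**Working it through.** **Inputs from the protocol.** Improvement of 5 points (placebo) and 15 points (diclofenac) at 4 weeks, so a difference of 10; SD of change 17; two-sided alpha 0.05; 46 per group required; 100 recruited 1:1, so 50 per arm.

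**Assumptions not in the protocol.** Compound symmetry across the three visits; per-visit SD s of 15 to 20; true week-12 difference x of 0, 5 or 10 points. Because 17² = 2s²(1 − ρ), the implied between-visit correlation is ρ = 1 − 17²/(2s²): 0.36 at s = 15, 0.50 at s = 17 and 0.64 at s = 20.

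**1. The plan's own figure.** n = 2(1.960 + 0.842)² × 17²/10² = 45.4, so 46 per group. By the exact noncentral t, the noncentrality at 46 is 10/(17√(2/46)) = 2.82 and the power 79.7%. At 50 it is 2.94 and the power 83.0%. The stated figure reproduces.

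**2. What each named effect estimates.** Write the true differences between arms at weeks 0, 4 and 12 as 0, 10 and x.

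- Hypothesis: 10 − 0 = 10.
- Time effect: arms combined, so the treatment difference does not enter.
- Treatment main effect: (0 + 10 + x)/3, which is 3.33, 5.00 or 6.67 for x = 0, 5 or 10.

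**3. Power of the treatment main effect, 50 per arm.** The SD of a person's three-visit mean is s√((1 + 2ρ)/3): 11.3, 13.9 and 17.4 for s = 15, 17 and 20. The noncentrality is the effect divided by (that SD × √(2/50)), with 98 df.

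| Week-12 difference | s = 15 | s = 17 | s = 20 |
|---|---|---|---|
| 0 (gone) | 31% | 22% | 16% |
| 5 (halved) | 59% | 43% | 30% |
| 10 (sustained) | 83% | 66% | 47% |

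If the difference grew to 15 points by week 12, the range would be 66-95%.

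**4. Power of the interaction, which is not named.** Here s²(1 − ρ) = 17²/2 = 144.5 whatever ρ is, and λ = 25 × (sum of squared deviations of the three differences from their mean)/144.5, on 2 and 196 df.

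- x = 0 or 10: λ = 25 × 66.7/144.5 = 11.5, power 86%.
- x = 5: λ = 25 × 50/144.5 = 8.65, power 75%.
- No difference at week 4 and 10 points at week 12: λ is again 11.5 and power 86%.

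So even the interaction does not isolate week 4.

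**5. Time effect with no drug effect.** If both arms gain the placebo arm's 5 points at week 4 and keep them at week 12, λ = 100 × 16.7/144.5 = 11.5, and the time effect is significant 86% of the time. If the gain halves to 2.5 points by week 12, λ = 100 × 12.5/144.5 = 8.65, and the figure is 75%. The protocol gives the 5 points for week 4 only.

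**6. Baseline-adjusted comparison at 4 weeks.** The residual SD is s√(1 − ρ²): 14.0, 14.7 and 15.4 for s = 15, 17 and 20. Power at 50 per arm is 94%, 92% and 90%.

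**The case against.** The strongest reply is that Section 12 is loosely worded rather than wrong. It does not call the ANOVA primary. One sentence serves both aims, which explains the three visits. The primary time point is fixed elsewhere, and the sample-size text points to a t-test on 4-week improvement. Model terms and contrasts are often set out in a statistical analysis plan. Part of this stands: the authors may well have meant an interaction or a 4-week contrast. But the protocol does state a test for its primary outcome, gives no other, and that test disagrees with its own hypothesis. This is therefore not a detail left for later.

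Several stronger readings are tempting, and the document does not support them:

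- **That the ANOVA lacks 80% power.** This depends on a correlation and a week-12 effect that the protocol does not give. The main effect reaches 83% in one scenario above and up to 95% if the difference grows to 15 points. The interaction reaches 86% in two of its three scenarios.
- **That a significant time effect would count as success.** Section 5 requires greater improvement than on placebo, so a pooled time effect would not meet the hypothesis. The fault is that Section 12 does not rule it out.
- **That people without a week-12 score would be lost.** This follows only if a complete-case ANOVA is used. The protocol does not state how missing visits are handled.
- **That omitting baseline as a covariate is an error.** A comparison of change scores is valid in a randomised trial and matches the sample-size calculation. ANCOVA is the more efficient choice.

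**Conclusion.** The mismatch is certain and rests on the protocol's text alone: neither effect named in Section 12 is the between-group difference in VISA-A improvement at 4 weeks. The sample size of 46 per group is right for the test it names. For the ANOVA, the 80% is not established, and for the treatment main effect it is probably lower. That effect exceeds 80% in only one of the nine scenarios tabulated, the one with a fully sustained effect and the smallest SD. These power figures are illustrations that rest on the assumed per-visit SD, compound symmetry and week-12 difference; they are not properties of the plan. The point should be settled before unblinding, because it decides which result answers the trial's main question.

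**What to change.** Rewrite the VISA-A sentence in Section 12 to:

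- name the between-group comparison of VISA-A at 4 weeks as the primary test, preferably ANCOVA of the 4-week score on treatment with baseline VISA-A as covariate, including everyone with a 4-week score. The 4-week treatment contrast from a baseline-adjusted repeated-measures model would target the same difference, and a two-sample comparison of 4-week change would be the minimum that matches the sample size;
- report the adjusted difference with its 95% confidence interval;
- make week 12 a secondary contrast for Aim 2;
- state that the 46 per group refers to the 4-week comparison.

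The cost is one paragraph. Baseline VISA-A is already collected at Visit 1, so no new data, visits or participants are needed.

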## **Visit 1 – Week 0**

Consent will be obtained by [name]. EB will complete the eligibility screen, which includes data collection (demographic information, BMI, rehabilitation history, and medical questionnaire including date of last NSAID taken). Subjects will complete the VISA-A questionnaire (a self-report questionnaire which measures Achilles tendinopathy severity). The investigator will use the MyotonPro to assess the transverse tendon stiffness at the location of maximal tendon thickening, and will use the AlgoMed Algometer to assess the subject's pain pressure threshold (PPT) on the most affected area of the Achilles tendon. Testing will be conducted at a controlled rate (30 KPa/s) with the subject lying prone on a treatment plinth. Pressure is gradually applied until the subject first experiences onset of pain, at which point they push a button. In rare cases where the person with CAT has baseline (resting) pain, then they will be instructed to press the button at the first increase in pain.

Subjects will then be issued with either placebo or 10% diclofenac gel. The gel will be supplied by a pharmacist, and the investigator and subject will not know the identity of the tubes. Subjects will be instructed to massage 1 gm of gel on the most painful area of the tendon for 30 - 45 seconds. The subject will also be instructed to how often to apply the gel (every 8 hours/3 times a day for 4 weeks) before the next scheduled appointment. They will be asked to complete a medication administration diary to confirm their compliance with the regimen, to document any medical or paramedical treatments received, and an exercise diary to record their exercise and physical activities.

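### The 4-week VISA-A comparison is left unadjusted for baseline, so the planned analysis can only match or fall short of the precision of a baseline-adjusted one

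*Protocol*

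**What the plan says.** The primary outcome in section 10.1 is "VISA-A score (0-100) at 4 weeks". The hypothesis in section 5 is put in terms of change: "Individuals treated with topical diclofenac will have a greater improvement in VISA-A score at 4 weeks than those treated with placebo gel".

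Section 12 names one analysis for this outcome: "A repeat measures ANOVA will be used to detect the effect of time (0, 4, 12 weeks". The randomised arm is the other factor, and week 0 is one of three levels of the time factor. The protocol names no covariate and no constraint that the arms share a baseline mean.

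The baseline value is available for everyone. At Visit 1, before gel is issued, "Subjects will complete the VISA-A questionnaire".

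The sample size calculation is also on the change scale. It takes a mean gain of 5 points with SD 17 for the placebo arm and sets against it the figure for the active arm: "compared to a clinically significant improvement of 15 (SD17) with diclofenac". It arrives at 46 per group for a two-sided t-test at alpha 0.05 and power 0.80. Section 8 plans to recruit 100 participants.

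**The concern.** In a repeated measures ANOVA with week 0 among the responses and a separate baseline mean for each arm, the treatment contrast at week 4 is the difference between arms in mean change from baseline. This subtracts the whole of any chance baseline difference, as if the regression of week-4 on baseline score had slope 1. Adjusting for baseline as a covariate estimates that slope from the data and has, in large samples, a variance no greater than that of the change score.

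At stake is precision. The calculation asks for 46 per group and recruitment gives 50 per group at 1:1, so the trial sits close to its stated 80% power. A measurement already taken from every participant could narrow the confidence interval without recruiting anyone.

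**Working it through.** **Inputs from the protocol.** Difference in mean improvement 15 − 5 = 10 points; SD of improvement 17 in each arm; two-sided alpha 0.05; power 0.80; 46 per group required; 100 recruited at 1:1, so 50 per group.

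**Assumed inputs.** The correlation rho between week-0 and week-4 VISA-A, and the SDs s0 and s4 at those weeks, are not in the protocol. They are varied below with the SD of change held at 17.

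**The plan's own figure.** The normal approximation gives n = 2 × [(1.96 + 0.84) × 17/10]² = 45.4 per group (unrounded normal quantiles), rounded up to 46. The noncentral t gives 46.35. Power by noncentral t is 79.7% at 46 per group and 83.0% at 50. The stated 46 reproduces.

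**Variance per participant, equal residual variance in the two arms.**

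- Change score: s0² + s4² − 2·rho·s0·s4
- Week-4 score adjusted for baseline: s4²(1 − rho²)
- Difference: s0² − 2·rho·s0·s4 + rho²·s4² = (s0 − rho·s4)²

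The difference is a square, so it is never negative. It is zero when rho = s0/s4. Adjustment costs one degree of freedom, which is negligible at this size.

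**Equal SDs (s4 = s0).** The ratio of adjusted to change-score variance is (1 − rho²)/[2(1 − rho)] = (1 + rho)/2, so the residual SD is 17 × √[(1 + rho)/2].

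| rho | Variance reduction | Residual SD | Power, 46 per arm | Power, 50 per arm |
|---|---|---|---|---|
| change score | – | 17.0 | 80% | 83% |
| 0.3 | 35% | 13.7 | 93% | 95% |
| 0.5 | 25% | 14.7 | 90% | 92% |
| 0.7 | 15% | 15.7 | 86% | 88% |
| 0.8 | 10% | 16.1 | 84% | 87% |
| 0.9 | 5% | 16.6 | 82% | 85% |

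A simulation of 5,000 trials with 46 per arm gave variance ratios of 0.65, 0.77 and 0.86 at rho 0.3, 0.5 and 0.7, against 0.65, 0.75 and 0.85 from the formula. Both estimators averaged 10 points to within 0.03, so neither is biased.

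**Unequal SDs.** Entry requires a VISA-A score below 80 (section 9). That cap limits the spread at week 0 but not at week 4. Taking s4 = 1.25 × s0 as an illustration, in units of s0²:

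| rho | Change score, 2.5625 − 2.5·rho | Adjusted, 1.5625(1 − rho²) | Variance reduction | Power, 46 per arm |
|---|---|---|---|---|
| 0.3 | 1.8125 | 1.4219 | 22% | 88% |
| 0.5 | 1.3125 | 1.1719 | 11% | 84% |
| 0.7 | 0.8125 | 0.7969 | 2% | 80.5% |
| 0.8 | 0.5625 | 0.5625 | 0% | 80% |

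**The case against.** The strongest defence is that nothing here is an error. The hypothesis concerns improvement, the sample size is built on improvement, and the change contrast estimates exactly that without bias under randomisation. This stands. The point concerns efficiency only.

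A second defence is that having baseline among the outcomes does not in itself waste information. This also stands: a longitudinal model that constrains the arms to a common baseline mean recovers about the same precision as ANCOVA. The loss comes from leaving the two baseline means unconstrained, and section 12 states no such constraint.

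A third is that a statistical analysis plan, not shown here, could add the covariate. It could, but it would have to depart from a model in which the protocol has already placed week 0 on the outcome side.

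Two stronger readings are tempting and not supported. A reader might infer that adjustment gives a smaller variance at every correlation below 1. That needs equal SDs at weeks 0 and 4, which the protocol does not give and the entry cap makes doubtful; otherwise the variance is only never larger. The same condition governs any claim that a change score over-corrects for chance imbalance. A reader might also infer that adjustment secures 80% power against losses. No dropout rate is stated, and the gain may be nil. At an illustrative 42 per arm the change score has 76% power. Adjustment gives 91% at rho 0.3 with equal SDs, but 78% at rho 0.9 with equal SDs, and 76% at rho 0.8 with an SD ratio of 1.25.

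Finally, section 12 does not say which ANOVA term tests the 4-week hypothesis. The comparison here takes the most favourable reading, that the week-4 contrast is used.

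**Conclusion.** The point holds as a worthwhile, low-cost improvement. The planned 4-week contrast is unbiased and the 46 per group is right for it, so neither should be reported as a mistake. The direction is certain: apart from one degree of freedom, the contrast is never more precise than the baseline-adjusted comparison.

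The size is uncertain. Across the scenarios shown, the variance reduction runs from none to 35%, and power at 46 per arm from about 80% to 93%. These figures assume an SD of change of 17, a true difference of 10 points, equal residual variance in the two arms, and either equal SDs at the two visits or the 1.25 ratio shown. The correlation and the visit-specific SDs are assumptions throughout.

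**What to change.** In section 12, make week-4 VISA-A the outcome, with treatment as factor and baseline VISA-A as covariate. Equivalent choices are a mixed model of weeks 4 and 12 with baseline as covariate, or a longitudinal model of all three visits that constrains the arms to a common baseline mean. Name the 4-week treatment contrast as the primary test and the 12-week contrast as the test for Aim 2 in section 3.

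Keep the sample size, and describe the t-test calculation as taking no credit for baseline adjustment.

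The cost is wording only. Baseline VISA-A is already collected at Visit 1, and neither enrolment nor visits change.

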## **3. Aims of Study**

1. To determine whether a 4-week course of 10% topical diclofenac improves clinical outcome (VISA-A score) relative to placebo.
2. To determine whether any improvements seen with diclofenac compared to placebo persist 8 weeks later (i.e. 12 weeks from baseline)

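### The planned VISA-A test (main effect of time or of treatment over weeks 0, 4 and 12) is not the week-4 difference in improvement that the trial hypothesises and is powered for

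*Protocol*

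**What the plan says.** The protocol states the question consistently in three places.

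- Section 5 (Hypothesis): "Individuals treated with topical diclofenac will have a greater improvement in VISA-A score at 4 weeks than those treated with placebo gel".
- Section 10.1 (Primary Outcome): "VISA-A score (0-100) at 4 weeks".
- Sample Size Calculation: "the placebo group will experience a clinically insignificant mean improvement of 5 (SD17) points on the VISA-A", set against 15 points (same SD) on diclofenac, and then "For a two-sided t-test with alpha 0.05 and power 0.80, the required sample size is 46 per group".

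Section 3 adds a separate second aim: whether any advantage over placebo is still present at 12 weeks.

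The only VISA-A analysis described is in section 12 (Statistical Considerations and Data Analysis): a repeated-measures ANOVA to "detect the effect of time (0, 4, 12 weeks) or treatment (placebo vs active) on VISA-A score". That section names no treatment-by-time term, no week-4 contrast and no comparison of change scores between arms. The two-sample t-test used for the sample size does not reappear as an analysis of VISA-A.

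**The concern.** In a repeated-measures ANOVA with two arms and visits at 0, 4 and 12 weeks, the two effects that section 12 names answer other questions.

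- **Time** asks whether VISA-A changed in the two arms taken together. It does not compare treatments.
- **Treatment** asks whether the arms differ on the mean of the three visits. The baseline visit contributes an expected difference of zero, and the week-12 visit contributes whatever remains eight weeks after the gel is stopped. The week-4 effect counts for one third.

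The hypothesis needs the arm difference in change from week 0 to week 4. Aim 2 needs the same for week 0 to week 12. Under the stated test, a drug that works exactly as assumed at week 4 can be missed, and its size at week 12 is folded into the same term. It is also unclear which p-value is the primary result: time, treatment, or an unnamed interaction that the software will print anyway.

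**Working it through.** **Inputs from the protocol.** Week-4 improvement of 5 vs 15 points (difference 10); SD of improvement 17; two-sided alpha 0.05; power 0.80; 46 per arm required; 100 to be recruited 1:1, so 50 per arm.

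**Assumptions not in the protocol.** Equal correlation rho between visits (0.3, 0.5, 0.7); equal SD at each visit; no expected baseline difference; a week-12 arm difference d12 of 0, 5 or 10 points; complete data.

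**Step 1: the stated sample size.** n per arm = 2 × [17 × (1.960 + 0.842) / 10]² = 45.4, rounded up to 46. The figure reproduces. Noncentral-t power of the week-4 change comparison is 79.7% at 46 per arm and 83.0% at 50 (SE = 17 × √(2/50) = 3.4; 10/3.4 = 2.94).

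**Step 2: the treatment main effect.**

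- Expected difference: (0 + 10 + d12)/3 = 3.3, 5.0 or 6.7 points.
- Visit SD that keeps the SD of change at 17: σ = 17/√[2(1 − rho)] = 14.4, 17.0, 21.9 for rho 0.3, 0.5, 0.7.
- SD of a participant's three-visit mean: σ√[(1 + 2rho)/3] = 10.5, 13.9, 19.6.
- Power from the noncentral t:

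| rho | n per arm | d12 = 0 | d12 = 5 | d12 = 10 |
|---|---|---|---|---|
| 0.3 | 46 | 33% | 62% | 85% |
| 0.3 | 50 | 35% | 66% | 88% |
| 0.5 | 46 | 21% | 40% | 63% |
| 0.5 | 50 | 22% | 43% | 66% |
| 0.7 | 46 | 13% | 23% | 36% |
| 0.7 | 50 | 13% | 24% | 39% |

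Simulation at 46 per arm and rho 0.5 gave 20%, 41% and 62% for the main effect and about 80% for the week-4 change test, in line with the formulas.

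**Step 3: the time effect when the drug does nothing.** Suppose both arms gain 5 points by week 4 and hold them. The squared deviations of (0, 5, 5) from their mean sum to 16.67. The within-subject error variance is σ²(1 − rho) = 17²/2 = 144.5 whatever the value of rho. With 100 participants the noncentrality is 100 × 16.67/144.5 = 11.5 on 2 and 196 df, and the time effect is significant in about 86% of trials. With 92 participants it is 83%.

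**Step 4: the treatment-by-time interaction, which section 12 does not name.** Noncentrality is (n/2) × (sum of squared deviations of 0, 10, d12)/144.5. The sums are 66.7, 50.0 and 66.7 for d12 = 0, 5, 10. At 46 per arm the noncentrality is 10.6, 8.0 and 10.6, and power is 83%, 71% and 83%. At 50 per arm power is 86%, 75% and 86%. These do not depend on rho.

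**The case against.** The strongest reply is that the sentence in section 12 names the two factors of a time-by-treatment ANOVA, not a closed list of tests, and that such a model ordinarily includes the interaction. On that reading power is much better, as step 4 shows. But the sentence says what the analysis is meant to detect, and it joins two main effects with the word *or*. The interaction, moreover, is a 2-df test that any pattern of difference across the three visits can trigger. It is not specific to week 4, and it falls to 71–75% if half the difference remains at week 12. So the stated 80% does not carry over on this reading either.

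A second reply is that a statistical analysis plan could name the contrast, since the target is clear elsewhere in the protocol. That would answer silence. Here the protocol names effects that do not match its own hypothesis.

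Several narrower objections stand:

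- The power range rests on a correlation and a week-12 effect that the protocol does not give, and one of the nine scenarios (rho 0.3, full persistence) exceeds 80%. If the difference grew to 15 points by week 12, power at 46 per arm would be 97%, 81% and 52% for rho 0.3, 0.5 and 0.7. The right statement is that the power is undetermined, not that it is always too low.
- The 86% in step 3 is correct detection of a real change in both arms. It misleads only if a time effect is read as evidence for the drug.
- Chance baseline imbalance is not a reason to prefer a change score. It enters the three-visit mean with weight 1/3, but the change score with weight −1. Allowing for correlation, each point of imbalance shifts the two by (1 + 2rho)/3 and −(1 − rho): 0.67 and −0.50 at rho 0.5, 0.53 and −0.70 at rho 0.3. Adjusting for baseline deals with this.
- VISA-A is collected at every visit, so visit-specific estimates remain possible. The plan simply does not commit to them.
- Sizing with a t-test and analysing with a longitudinal model is acceptable, provided the model tests the same comparison.

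**Conclusion.** The concern holds. The sample-size arithmetic is right, but it belongs to a week-4 between-arm comparison of improvement that section 12 does not plan. The treatment effect it does plan carries 3.3 to 6.7 of the assumed 10 points. Its power at 50 per arm is 13% to 88% over rho 0.3 to 0.7 and a week-12 difference of 0 to 10, against 83% for the week-4 comparison; at 46 per arm the figures are 13% to 85% against 79.7%. All of these assume equal correlation between visits, an SD of change of 17 and no missing data. The conclusion that the stated power does not apply to the named test does not depend on which scenario is true. Because this sentence decides which result is primary, it should be corrected before the analysis.

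**What to change.** In section 12, state one primary test: the between-arm difference in VISA-A change from baseline to week 4, two-sided 5%, reported with its 95% CI. It can be a single contrast from a repeated-measures model with treatment-by-time terms, or a comparison of week-4 scores adjusted for baseline. Make the corresponding week-12 contrast the secondary test for Aim 2. Add that the main effects of time and treatment are not tests of the hypothesis.

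The cost is a few lines in the protocol and, if there is one, the SAP. Data collection and enrolment do not change, and the existing 46 to 50 per arm then supports the stated power of about 80%.
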